#### 2.8.2. Control Condition

Participants in the control group will continue their usual lifestyle or receive usual care rehabilitation during the study period, with no additional intervention. They will be encouraged to maintain their usual activities and avoid participation in other structured exercise programs outside the study intervention. The type, frequency, and intensity of concurrent treatments will be recorded and treated as covariates in the statistical analysis to control for potential confounding effects. After the 12-week period, they will be invited to participate in the intervention program according to their preference. Participants will be asked to inform the research team if there are any routine changes or unexpected events (e.g., hospital admission, illness).

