## 2. Materials and Methods

### 2.1. Aims

The purpose of this study is to investigate the effectiveness of the web-based physical–cognitive telerehabilitation exergaming on the physical function and cognitive performance of chronic stroke survivors as compared to the control condition.

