### 2.6. Randomization and Allocation Concealment

Eligible participants will be randomly allocated to the intervention or control group in a 1:1 ratio. Randomization will be performed by an independent researcher using a computer-generated randomization sequence created with SPSS version 25. Allocation concealment will be ensured using sealed, opaque, and sequentially numbered envelopes, which will be opened only after baseline assessment and participant enrolment. All outcome assessments will be conducted by trained assessors who are blinded to group allocation. Due to the nature of the intervention, neither the physiotherapist delivering the intervention nor the participants can be blinded.

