### 2.9. Intervention Adherence and Adverse Events

Participants in the intervention program will have their training sessions automatically recorded on the ExerbrainCMU web-based platform immediately after each exercise session, including information on session duration, training completion, and training frequency. These data will be used to monitor adherence and engagement throughout the intervention period. Weekly reminders will be sent via social media applications (e.g., LINE and Facebook) to promote adherence. In addition, research staff will conduct scheduled telemonitoring sessions at weeks 2, 4, 8, 10, and 12, during which information regarding participants’ training will be collected and cross-validated with the platform records.

Participants will be instructed to report any adverse events that occur during the study. They will also be asked about any health problems at each assessment point from baseline to 12 weeks. Participants will be informed that they can contact the research team at any time if they have questions or concerns. All adverse events or harms associated with the intervention will be recorded and reported in the study findings.

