
### 2.11. Statistical Analyses

Descriptive statistics will be used to summarize the demographic data and baseline characteristics of each group. Data normality will be assessed using the Kolmogorov–Smirnov test. Homogeneity of variances will be evaluated using Levene’s test. Independent-samples *t*-tests and chi-square tests will be used to compare demographic characteristics between the intervention and control groups. The primary analysis will be conducted using a two-way mixed-model ANOVA to examine differences in outcome measures between groups across two assessment time points (baseline and 12 weeks). The Bonferroni correction will be used for the post hoc analysis. In case of baseline imbalances, an analysis of covariance (ANCOVA) will be conducted to compare post-intervention outcome measures between groups, with baseline scores and time since stroke included as covariates to control for potential confounding effects. However, if data are not normally distributed, appropriate nonparametric methods will be considered. The primary comparative analyses will follow the intention-to-treat principle. Missing data will be handled using multiple imputation by chained equations, generating five imputed datasets. The imputation model will include all outcome variables, baseline scores, and relevant covariates. Additionally, a per-protocol analysis will be performed for the primary outcomes to evaluate the intervention effects among participants who attended at least 80% of the sessions. Statistical significance will be set at *p* < 0.05.

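### Section 2.8.2 makes concurrent treatments covariates against confounding, but follow-up treatment cannot confound a randomised contrast and is in neither model of section 2.11

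*Protocol article*

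**What the plan says.** Section 2.8.2 (Control Condition) lets controls carry on with their usual lifestyle or usual rehabilitation and then states: "The type, frequency, and intensity of concurrent treatments will be recorded and treated as covariates in the statistical analysis". The same sentence gives control of possible confounding as the purpose. It sets no condition and does not say that only baseline values are meant.

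Section 2.11 (Statistical Analyses) describes the outcome models. First: "The primary analysis will be conducted using a two-way mixed-model ANOVA to examine differences in outcome measures between groups", over baseline and 12 weeks, with no covariate named. Second, if there is baseline imbalance, an ANCOVA "with baseline scores and time since stroke included as covariates to control for potential confounding effects". Covariates are otherwise mentioned in that section only for the imputation model. It also says: "The primary comparative analyses will follow the intention-to-treat principle".

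Section 2.1 (Aims) sets the target as effectiveness "on the physical function and cognitive performance of chronic stroke survivors as compared to the control condition". Section 2.6 has envelopes opened after baseline assessment, and concedes that "neither the physiotherapist delivering the intervention nor the participants can be blinded".

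**The concern.** A confounder of a treatment comparison is a common cause of treatment and outcome. Here treatment is set by a concealed 1:1 random sequence, so nothing that happens afterwards can be a cause of it. Treatment received during follow-up can instead be a consequence of allocation. A participant who trains three hours a week on the exergame, and knows it, may drop outside therapy; a control who knows that nothing extra is coming may seek it.

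Adjusting for such a variable can do two things. It can remove from the estimate the part of the effect of assignment that runs through outside treatment. And if something unmeasured drives both uptake and outcome, it can create an association between arm and outcome that randomisation had excluded. Either way the result need not be the effect of being assigned to the exergame rather than to the control condition. The sentence also commits the trial to covariates that the analysis section does not contain.

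**Working it through.** **The texts side by side**

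| Place | Covariates in the outcome model |
|---|---|
| 2.8.2 | type, frequency and intensity of concurrent treatments |
| 2.11, primary mixed ANOVA | none named |
| 2.11, ANCOVA if baseline imbalance | baseline scores, time since stroke |

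Concurrent treatments appear in neither model of 2.11. The plan gives no figure on this point, so there is none to reproduce. The sample size (46, raised to 52) is not in question.

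**Illustration 1: outside treatment differs by arm**

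From the document: 46 participants after dropout (2.5), so 23 per arm. Assumed, because the document gives no values: exergame effect apart from outside treatment 0.75 SD; benefit of outside treatment 0.4 SD; uptake 20% in the exergame arm and 40% in controls; uptake unrelated to prognosis; baseline-outcome correlation 0.6; three covariates for type, frequency and intensity.

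- Effect of assignment = 0.75 + 0.4 × (0.20 − 0.40) = 0.75 − 0.08 = 0.67 SD.
- Simulation, 20,000 trials: mean estimate 0.674 without the covariates and 0.748 with them.
- Uptake reversed (40% exergame, 20% control): 0.75 + 0.4 × 0.20 = 0.83 SD. Simulated: 0.835 without, 0.763 with.

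The unadjusted estimate recovers the effect of assignment in both cases. The adjusted estimate stays near 0.75 and is too large in one case and too small in the other.

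**Illustration 2: a shared unmeasured cause**

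All inputs are assumed except N = 52: direct effect 0.74; allocation to the exergame lowers concurrent treatment by *a* SD; concurrent treatment acts on outcome with coefficient *b*; an unmeasured factor loads *u* on concurrent treatment and 0.5*u* on outcome. Then:

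- effect of assignment = 0.74 − *a b*
- expected adjusted estimate = 0.74 + *a* × *u* × 0.5*u*

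| *a* | *b* | *u* | Effect of assignment | Simulated unadjusted | Simulated adjusted |
|---|---|---|---|---|---|
| 0 | 0.3 | 0 | 0.74 | 0.743 | 0.742 |
| 0 | 0.3 | 0.5 | 0.74 | 0.744 | 0.742 |
| 0.5 | 0.3 | 0 | 0.74 − 0.15 = 0.59 | 0.594 | 0.743 |
| 0.5 | 0 | 0.5 | 0.74 | 0.740 | 0.804 |
| 0.5 | 0.3 | 0.5 | 0.59 | 0.591 | 0.802 |

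(4,000 runs per row.) For the last two rows the formula gives 0.74 + 0.5 × 0.5 × 0.25 = 0.8025, in agreement with the simulation.

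Rows 1 and 2: if allocation does not change concurrent treatment, leaving it out causes no bias, so there was no confounding to control. Row 3: adjustment removes part of the effect of assignment. Row 4: adjustment adds bias even though concurrent treatment has no effect on outcome.

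**The case against.** **Part of usual care may predate allocation.** Participants are at least 6 months past their stroke, and controls continue what they already do. This stands: rehabilitation at enrolment is a legitimate covariate. But the sentence does not restrict itself to that level, and treatment described as concurrent is most naturally treatment during the trial.

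**The article is condensed and an analysis plan may settle the models.** An unlisted detail would be no finding. Here the article states both the use of these covariates and a reason for it, and the reason is wrong whatever another document adds.

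**A reader might infer that the document sets two rival primary models, to be chosen between once results are known.** That goes too far. Section 2.11 expressly names the mixed ANOVA as primary, while 2.8.2 speaks only of the statistical analysis in general. What remains is a mismatch between the sections.

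**A reader might also infer that only controls are asked to avoid other exercise**, since this stands under the control condition: "They will be encouraged to maintain their usual activities and avoid participation in other structured exercise programs outside the study intervention". The closing words fit advice to both arms at least as well, so it may be loose placement. The point does not rest on it; open-label allocation is enough for uptake to differ.

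**The sponsor may want a comparison free of uneven outside care.** That is a fair question but a different one. Answering it needs the assumption that nothing unmeasured drives both uptake and outcome, which the trial data cannot check. It belongs in an exploratory analysis.

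**Conclusion.** The point holds and should be fixed, though it does not undermine the trial. The rule in 2.8.2 has a mistaken rationale, is not limited to pre-randomisation values, and is not carried into 2.11. If followed with follow-up data, it can move the estimate away from the effect of assignment.

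How far, and in which direction, cannot be derived from the document. With a 20-point difference in uptake and a benefit of 0.4 SD, both assumed, the shift is about 0.08 SD: 0.67 against 0.75 when exergame participants use less outside treatment, and about the same amount the other way when they use more. If uptake is the same in both arms and allocation does not affect it, the two estimates agree on average. A reader might take the illustrations as a forecast that the result will be exaggerated; nothing in the document supports a particular direction.

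**What to change.** In 2.8.2, keep the commitment to record concurrent treatments and delete the rest of that sentence, from the words making them covariates through the stated purpose. Section 2.11 then alone defines the primary model.

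Record type, frequency and intensity in both arms with the same questions at the same times, and report them by arm. The contacts in 2.9, where "research staff will conduct scheduled telemonitoring sessions at weeks 2, 4, 8, 10, and 12", are described for the exergame arm's training, so they are not by themselves a common schedule. Label any model adjusted for follow-up treatment exploratory. If adjustment for rehabilitation is wanted, name its level at enrolment, recorded before randomisation, as the covariate in 2.11.

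Cost: a wording change and slightly more recording. Recruitment began in February 2026, so participants already enrolled may lack some of these data. The sample size stays at 52 and no power is given up: in the simulation with equal uptake (30% in each arm), power of the mixed ANOVA was about 78% without the three covariates and 76 to 77% with them.

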### 2.9. Intervention Adherence and Adverse Events

Participants in the intervention program will have their training sessions automatically recorded on the ExerbrainCMU web-based platform immediately after each exercise session, including information on session duration, training completion, and training frequency. These data will be used to monitor adherence and engagement throughout the intervention period. Weekly reminders will be sent via social media applications (e.g., LINE and Facebook) to promote adherence. In addition, research staff will conduct scheduled telemonitoring sessions at weeks 2, 4, 8, 10, and 12, during which information regarding participants’ training will be collected and cross-validated with the platform records.

Participants will be instructed to report any adverse events that occur during the study. They will also be asked about any health problems at each assessment point from baseline to 12 weeks. Participants will be informed that they can contact the research team at any time if they have questions or concerns. All adverse events or harms associated with the intervention will be recorded and reported in the study findings.

### 2.10. Assessment and Outcome Measures

Comprehensive health outcomes, including motor function, fall risk, gait speed, balance, limits of stability, muscle power, weight distribution, body composition, executive function, global cognitive function, memory, attention, and enjoyment, will be assessed by trained assessors blinded to participants’ group allocation. Physical and cognitive parameters will be assessed at baseline and the end of the 12-week exercise, while enjoyment rating scores will be determined after 1 week and 12 weeks of intervention. There will be one assessor for each assessment category (cognition and physical function). The assessment sessions will be divided into two days. For the first day, memory, attention, motor performance, gait speed, and fall risk will be measured. For the second day, body composition, global cognitive function, executive function, balance, limits of stability, muscle power, and weight distribution will be determined. An overview of the schedule of enrolment, interventions, and assessments is summarized in Table 1.

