### 2.7. Procedure

Participants will be recruited through both online and offline advertisements within local communities. Written informed consent will be obtained from eligible participants before participation in the study. All participants will be assessed for physical function (motor function, gait speed, balance and limits of stability, fall risk, muscle power, and weight distribution) and cognitive performance (global cognitive function, executive function, memory, and attention). Physical and cognitive performances will be assessed at baseline and after the end of 12 weeks of intervention. The enjoyment rating scores will be determined after 1 week and 12 weeks of training. A 12-week home-based training program will be implemented in this study. Participants will be encouraged to contact the research team whenever they have questions or concerns.

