Motor function, gait speed, balance and limits of stability, muscle power, and weight distribution will be assessed using the Motor Assessment Scale (MAS) [44], 10-Meter Walk test (10MWT) [45], the Modified Functional Reach Test (MFRT) [46,47], 5 times sit-to-stand test (5TSTS) [48], and the Stance Symmetry Test (SST) [49], respectively. For the MAS test, participants will be asked to perform 8 items of functional tasks: supine to side lying, supine to sitting, balance sitting, sitting to standing, walking, upper arm function, hand movement, and advanced hand activities. Each item is scored on a 7-point scale (0–6; 0 = no function to 6 = normal function), based on a person’s ability to perform specific tasks. Participants will perform each task three times and the best performance will be recorded. For the 10MWT, participants will be instructed to complete a 10 m walk at a self-selected speed with or without walking aids [45]. An acceleration distance of 2 m and a deceleration distance of 2 m will set up at the beginning and the rear end. The time will be recorded by digital stopwatch for the middle 10 m distance. Measurements will be determined twice. The speed will be calculated by dividing the distance by time (m/s). Dynamic balance and limits of stability while sitting will be measured by MFRT [46]. Participants will be sitting on a standard chair with their feet shoulder-width apart, flat on the floor, hips and knees at 90° flexion with the non-paretic side closest to the wall. The participant will be instructed to reach as far as possible with the arm horizontal while maintaining balance. The location of the fifth finger at the beginning and the end of the reach will be recorded. MFRT will consist of three conditions including forward reach while sitting with the unaffected side near the wall, lateral reach to the right while sitting with the back to the wall, and lateral reach to the left while sitting with the back to the wall. Each participant will perform a total of five trials per condition. The first two trials will be used for familiarization, and the mean of the final three trials will be used for analysis [46,47]. As for muscle power, participants will be instructed to perform five sit-to-stand repetitions as quickly as possible. The time required to complete the task will be recorded [48]. Weight distribution will be measured using the SST. This test assesses the distribution of weight between both legs. Participants will be instructed to stand with each foot on a separate weighing scale, with the distance between the feet set at 11% of the participant’s height. They will be asked to stand as still as possible for 30 s. The assessors will record the weight borne by each leg at 25 s. Each participant will complete three trials, and the results will be averaged. The symmetry ratio will be calculated as the average weight bearing through the affected leg divided by the average weight bearing through the non-affected leg [49]. Furthermore, minimum detectable difference (MDD) values for the MFRT, 5TSTS, and SST will be used to aid the interpretation of clinical significance. Body fat percentage and fat mass will be measured using a body fat composition monitor with an accuracy of 0.1 kg and 0.1%, respectively [50,51]. In addition, the Physical Activity Enjoyment Scale (PACES) will be used to assess participants’ enjoyment during the intervention [52]. PACES consists of eight items rated on a 7-point Likert scale from 1 (strongly disagree) to 7 (strongly agree). The overall enjoyment score will be derived from the sum of all item scores. Furthermore, adherence to the intervention will be recorded and calculated as the percentage of attended physical–cognitive training sessions using (n/36) × 100.

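### Blinded assessors are assigned the enjoyment scale, which rates the intervention after one week of training, so whoever collects it can learn the allocation before the week-12 TMT or TUG

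*Protocol article*

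**What the plan says.** Section 2.6 of the protocol article sets a general rule: "All outcome assessments will be conducted by trained assessors who are blinded to group allocation". It adds that neither the participants nor the treating physiotherapist can be blinded.

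Section 2.10 repeats the rule for a named list of outcomes. The list contains the two primary domains, executive function and fall risk, and ends with enjoyment: "attention, and enjoyment, will be assessed by trained assessors blinded to" participants' allocation. On staffing it says "There will be one assessor for each assessment category (cognition and physical function"). It then divides the tests over two days. Fall risk (TUG) falls on the first and executive function (TMT) on the second. Enjoyment is listed on neither.

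On timing, Section 2.7 says "The enjoyment rating scores will be determined after 1 week and 12 weeks of training", and Section 2.10 says "enjoyment rating scores will be determined after 1 week and 12 weeks of intervention". Table 1 agrees, with PACES after 1 week and at 12 weeks and no baseline value. Section 2.10.2 says what PACES measures: "enjoyment during the intervention".

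Under Section 2.8.2 the control group continues its usual lifestyle or usual care "with no additional intervention". It is offered the exergame programme only after the 12-week period.

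**The concern.** A rating of how enjoyable the training was carries information about who was trained. If the person who collects it also rates the outcomes, the stated blinding conflicts with the stated data collection. The first PACES contact comes well before the second and last measurement of TMT and TUG, so the knowledge would be in place when the post-intervention primary outcomes are taken.

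Participants and therapist know the allocation, so the assessor is the only safeguard against expectation entering the measurements. TUG, the 10-metre walk and five-times sit-to-stand are timed by the assessor. The Motor Assessment Scale is scored by the assessor, and reach distance is read by the assessor. Encouragement, the starting and stopping of a stopwatch, and scoring judgement can all drift towards the arm expected to improve.

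**Working it through.** The point rests on reading the sections together. The plan gives no figure to reproduce.

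**Step 1: who collects enjoyment.** Section 2.10 gives it to blinded assessors by name, and Section 2.6 makes no exception. The article names no separate collector and does not mention online self-completion.

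**Step 2: what the rating reveals.** PACES refers to the intervention (Section 2.10.2) and is timed from the start of training (Section 2.7). Controls receive no intervention before week 12 (Section 2.8.2). If only exergame participants are asked, being asked reveals the arm. If controls are asked as well, they must rate something they have not had, and their answers are likely to reveal the arm too.

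**Step 3: order in time.** PACES is first taken after week 1. TMT and TUG are taken at baseline and at week 12. The gap between first possible disclosure and final primary assessment is 12 − 1 = 11 weeks.

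**Step 4: which outcomes are exposed.** There is one assessor for cognition, which covers TMT, and one for physical function, which covers TUG. Enjoyment belongs to neither category. If one of the two collects PACES, either TMT or TUG is rated at week 12 by someone who may know the allocation. If both do, both outcomes are exposed. The text does not settle which.

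**Step 5: illustration of size.** Inputs:
- N = 46, the required total in Section 2.5
- two-sided alpha 0.05
- outcome SD scaled to 1
- baseline-to-week-12 correlation 0.5 (assumption)
- a shift at week 12 of 0.1 to 0.2 SD in favour of the exergame arm from unblinded rating (assumption; the article gives no figure)

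The planned primary analysis is the two-way mixed ANOVA. With two time points, its group-by-time test compares mean change between arms.

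- SD of change = √(2 × (1 − 0.5)) = 1.0
- SE of the difference = 1.0 × √(4/46) = 0.295
- Rejection probability with no true effect = 1 − Φ(1.96 − δ/SE) + Φ(−1.96 − δ/SE)

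| Assumed shift δ | δ/SE | Two-sided type I error |
|---|---|---|
| 0 | 0 | 5.0% |
| 0.1 SD | 0.339 | 6.3% |
| 0.2 SD | 0.678 | 10.4% |

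Under the ANCOVA that Section 2.11 reserves for baseline imbalance, the residual SD at the same correlation is √(1 − 0.5²) = 0.866. The SE is 0.866 × 0.295 = 0.255, and the corresponding figures are 6.8% and 12.3%. These use the normal approximation. They show how an assumed bias would carry through and do not estimate the bias itself.

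**The case against.** Several points on the other side are fair.

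- **Controls may be asked too.** The PACES row in Table 1 is not split by arm, and no sentence says controls are left out. That only the trained arm can answer is an inference from the wording on training and intervention. It is a reasonable one, and asking controls would not protect the blinding, but it remains an inference.
- **PACES is a self-rated questionnaire.** It has eight Likert items and need not be taken face to face, and the list in Section 2.10 may be loose wording. That stands as a possible explanation. An article may leave logistics to the full protocol, but here it says who assesses enjoyment, and what it says conflicts with blinding. If self-completion is intended, the sentence needs the same correction.
- **The primary outcomes are timed tests.** They leave less room for rater judgement than a scored scale. This limits the likely bias without removing it.

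A reader might also infer more than the text supports:

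- **That no unexposed assessor remains.** If one assessor collects PACES, the other need not be exposed, and a third collector is not excluded.
- **That the week-12 PACES unblinds between the two assessment days.** Enjoyment is assigned to neither day and could follow all the tests.
- **That the health questions unblind assessors.** Section 2.9 says "They will also be asked about any health problems at each assessment point from baseline to 12 weeks" without naming who asks.

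**Conclusion.** The point holds in a limited form. As written, Sections 2.6 and 2.10 require blinded assessors to collect a rating that can disclose allocation from week 1, before the week-12 primary outcomes. It could unblind the rater of TMT, of TUG, or of both. It does not show that either primary outcome will in fact be compromised, because the article does not say who collects PACES or how.

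The conclusion depends on two readings: that PACES refers to the exergame programme, and that one of the outcome assessors collects it, as Section 2.10 states. The type I error of about 6 to 10% is illustrative only. It depends on an assumed bias of 0.1 to 0.2 SD, an assumed correlation of 0.5, N = 46 and the planned mixed ANOVA. The textual conflict stands without it. The correction should be made, since assessor blinding is the trial's only blinding and cannot be restored once lost.

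**What to change.** 1. In Section 2.10, take enjoyment out of the list of outcomes rated by blinded assessors. In Section 2.6, state that the blinding rule covers all outcomes except PACES.
2. Have exergame participants complete PACES on the existing web platform, or have it collected by staff who do no outcome testing.
3. Keep the week-1 rating, and place the week-12 rating after both assessment days are finished.
4. State in Section 2.10.2 and Table 1 that PACES applies to the exergame arm only, and report it for that arm.

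The cost is a short form on a platform that already records each session, or a few minutes in the telemonitoring contacts that research staff already hold, plus the wording changes. No extra staff are needed, and no outcome or sample size changes. Recruitment began in February 2026, so the change should be made promptly.
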